### Participants

We will be collecting samples and data from two groups of patient participants (*n* = 200 in each group). Due to the cognitively vulnerable nature of the patient population and feasibility learning in relation to dementia diagnosis rates of our target population [22], we will seek proxy information about pre-fracture cognition to inform grouping allocation for analysis. Consequently, we will also seek written consent from “suitable informants” as defined by the inclusion criteria below, to complete the Informant Questionnaire for Cognitive Decline in the Elderly (IQCODE). The recruitment of a suitable informant for each patient is desirable, but not essential. The eligibility criteria for patient participants and suitable informant participants are as follows:

Patient inclusion criteria:

Group 1: ‘Confused’ hip fracture patients

**Inclusion Criteria:**
Patient must have had a confirmed proximal hip fracture requiring an operation and be aged 60 or older at the time of operation;Patient has a pre-operative Abbreviated Mental Test Score (AMTS) of 8 or below; or 4AT score of 1 or above;Patient must be undergoing spinal anaesthesia.

**Exclusion criteria:**
Decision taken not to have hip surgery;Patient has head trauma with bleeding as indicated by a CT scan;Patient has confirmed diagnosis of Parkinson’s disease;Patient not expected to survive beyond 4 weeks;Patient’s fall and subsequent hip fracture caused by acute Stroke, indicated by CT and/or MRI scan and/or clinical examination;Patient already enrolled in a Clinical Trial of an Investigational Medicinal Product (CTIMP).

Group 2: ‘Non-confused’ hip fracture patients

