Previous studies in older people with acute systemic inflammation have been limited by small sample sizes, the lack of adequate control groups and, in particular, have not assessed the impact of inflammation on recently emerging biomarkers of new brain injury [13].

One of the other difficulties encountered by research in this area is that hip fracture is an emergency and studies cannot directly collect pre-fracture data. However, well-validated methods for the assessment of pre-fracture cognitive ability are available. The Informant Questionnaire for Cognitive Decline in the Elderly (IQCODE [14] is one example widely-used clinically and for research purposes.

In the United Kingdom (UK) a significant proportion of hip fracture patients undergo surgery within spinal anaesthesia [15]. This routine clinical procedure involves inserting a needle into the patient’s spinal space (subarachnoid space) and injecting anaesthetic into the CSF. In this way, CSF can be collected just before the initiation of anaesthesia, using the same needle that will be used to administer the anaesthetic agent. This means that older patients undergoing emergency hip fracture repair surgery are a suitable group in which to measure systemic inflammation, brain inflammation and CSF markers of brain injury.

The impact of Acute SystematiC inflammation upon cerebRospinal fluId and blood BiomarkErs of brain inflammation and injury in Dementia: a study in acute hip fracture patients (ASCRIBED) will use the opportunity provided by hip fracture operations undertaken via spinal anaesthesia to investigate the impact of acute systematic inflammation upon CSF and blood biomarkers of brain inflammation and neuronal injury and on the exacerbation of dementia. We will collect samples from patients with and without dementia who are suffering a systematic inflammatory response (the ASCRIBED cohort). We will compare ASCRIBED’s ‘unstable’ groups (termed as to refer to the inflammatory response) with an existing cohort of patients living with dementia who have not experienced a systemic inflammatory response from an injury (henceforth known as the ‘Oslo’ cohort). The Oslo cohort will therefore provide ‘stable’ comparators. The study will shed light on the ability of acute inflammatory trauma to produce new brain injury in a vulnerable older population. The findings will then inform the search for new treatments targeting inflammation in dementia.

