#### Primary objective

To determine whether hip fracture patients living with dementia show elevated markers of brain inflammation in comparison to (1) stable patients living with dementia and (2) hip fracture patients without dementia, as measured by biomarkers in CSF. CSF inflammation will be measured by TNF-α, IL-1RA, IL-1β, IL-6 and brain injury and biomarkers will be measured by NfL, neurogranin, T-tau, synaptotagmin and SNAP-25.

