### Sample size

We will recruit 200 patients with dementia and hip fracture; and 200 patients without dementia but who have experienced a hip fracture. This sample size is pragmatically based upon what would appear to be achievable in the time available and with consideration of likely statistical power. Without adjustment, a sample size of 200 subjects per group will provide statistical power of 90% to detect a mean between group mean differences of 0.33 standard deviations in any outcome variable using a two-sided significance level of 5%. Assuming confounding variables entered into a General Linear Model ‘explain’ no more than 25% of the total variation (i.e. the co-efficient of determination, R2, is less than 0.25), then this sample size should provide 90%. Power to detect an ‘adjusted’ mean difference of around 0.37 residual standard deviations [27]. In either case, this would be deemed a relatively small effect to be detected with high probability.

Data will be collected initially from two different groups:
Group 1: Pre-operative acute hip fracture patients with confusion;Group 2: Pre-operative acute hip fracture patients without confusion.

In respect of Group 1 (those with confusion), the AMT (England) and 4AT (Scotland) score indicate that a patient may be living with dementia. However, this may not be confirmed until 1-month post-op when reviewing the patient’s case notes, contacting their GP or reviewing their relevant Suitable Informant’s IQCODE Scores. Based on prior research, we anticipate that up to 50% of patients who have an AMT score of 8 or less (England) or 4AT score of 1 or above (Scotland) will have dementia (diagnosed or undiagnosed/vectored) [22]. Therefore, up to 400 may need to be recruited to this group. Recruitment will be monitored and stopped for Group 1 as soon as we receive 200 patients with confirmed dementia required for the study.

We will also collect data from patients without confusion (Group 2), who are unlikely to be confirmed with dementia at 1-month post-op. These patients will be included in the non-dementia group. Again, recruitment will be monitored and stopped from this group once 200 non-dementia patients have been included. The number required from this group will be dependent upon the non-dementia confirmation rate for this group.

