#### Primary hypothesis

We will address the primary hypothesis, that systemic inflammation arising from hip fracture leads to an acute brain injury, by comparing the level of inflammatory and neuronal injury CSF and blood markers between the three groups defined above. Accordingly, we predict raised inflammatory and injury markers for the confirmed dementia-hip fracture group compared to the medically stable dementia group (Oslo cohort) and compared to the non-dementia hip fracture group.

Each of the markers will be compared across groups using a general linear model with the marker as the dependent variable (i.e. a separate model for each biomarker). The initial model will simply include group as an explanatory factor. A further model will then be constructed, including potential confounding variables, such as age, to provide an adjusted between group mean difference (comparing fracture patients with dementia to fracture patients without and fracture patients with dementia to stable dementia patients), together with 95% confidence intervals and significance test. In the event of the residuals for these models not appearing normally distributed, an appropriate transformation will be applied, such as a logarithmic transformation. We also predict that patients with dementia will have significantly worse cognitive and functional informant-based scores. A similar analysis will be conducted with cognitive and functional scores as the dependent variable.

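### Head trauma is excluded only when a CT shows bleeding and no listed item records head impact, so mechanical brain injury remains a rival explanation for raised injury markers, of unknown size

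*Protocol article*

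**What the plan says.** The exclusion lists for Group 1 and Group 2 carry the same head-trauma rule: "Patient has head trauma with bleeding as indicated by a CT scan". No other criterion covers head injury, and neither the criteria nor the data collection schedule asks for a scan. The stroke rule in the same lists accepts more kinds of evidence, since it applies to a fracture "caused by acute Stroke, indicated by CT and/or MRI scan and/or clinical examination". It reaches only a stroke that brought about the fall.

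The Primary objective section states that "biomarkers will be measured by NfL, neurogranin, T-tau, synaptotagmin and SNAP-25". The Primary hypothesis section gives the contrasts a causal reading, namely "that systemic inflammation arising from hip fracture leads to an acute brain injury". It plans an unadjusted model and then one "including potential confounding variables, such as age". The Oslo comparators are dementia patients "who have not experienced a systemic inflammatory response from an injury".

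Table 1 (sample and data collection schedule) has no entry for head impact, head CT or recent stroke. The one-month section has sites review the case notes and record further clinical data that it does not specify.

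**The concern.** The stroke rule speaks of a fall followed by a fracture, so the protocol itself treats falling as a mechanism of injury, and a fall can include a blow to the head. By excluding CT-proven bleeds and fall-causing strokes, the protocol already accepts that direct brain injury competes with inflammation as a cause of raised markers. The rule removes only the part of that injury that was scanned and bled.

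What is at stake is attribution. If some fracture patients have raised NfL, T-tau, neurogranin, synaptotagmin or SNAP-25 because they hit their heads, a group difference in these markers could be real and still not be due to systemic inflammation. A covariate that was never recorded cannot be adjusted for, however detailed the analysis plan is.

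**Working it through.** **The plan's own figure.** The Sample size section states that "a sample size of 200 subjects per group will provide statistical power of 90" per cent to detect 0.33 SD at a two-sided 5% level. The standard error of a difference is √(2/200) = 0.10 SD.
- Power at 0.33 SD: Φ(0.33/0.10 − 1.960) = Φ(1.34) = 0.910.
- Detectable difference at exactly 90% power: (1.960 + 1.282) × 0.10 = 0.324 SD.
- Adjusted, with R² = 0.25: (1.960 + 1.282) × √(2/(200 × 0.75)) = 0.374, against about 0.37 stated.

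The stated power reproduces and is not in question.

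**Who stays in, on a literal reading of the criteria.**

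| Situation | Status |
|---|---|
| Head impact, CT shows bleeding | Excluded |
| Head impact, CT clear | Eligible |
| Head impact, no CT | Eligible |
| Stroke that caused the fall (imaging or clinical examination) | Excluded |
| Recent stroke that did not cause the fall | Eligible |

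**Contrast with Oslo.** The Sample size section lists the assays run on the Oslo samples in 2017: three amyloid peptides and a ratio, YKL-40, four cytokines, and an item labelled G36-NG2. NfL, T-tau, synaptotagmin and SNAP-25 are not listed. G36-NG2 might be neurogranin, but the article does not say so. On the listed assays, at most one of the five injury markers can be compared.

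**Contrast between the fracture groups.** Final groups follow evidence of dementia (documented diagnosis or IQCODE), not confusion. Confused patients without such evidence go to the biobank, so the non-dementia group is drawn from the non-confused. Patients with dementia stay in whether confused or not. Let q be the share of patients without dementia who had an unexcluded head impact, and let c₁ and c₀ be their chances of pre-operative confusion with and without impact. The share left in the comparator is

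q(1 − c₁) / [q(1 − c₁) + (1 − q)(1 − c₀)],

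which is below q whenever c₁ > c₀. If head impact is otherwise equally common in people with and without dementia, the gap runs in the predicted direction. By this route alone it cannot exceed q.

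**Size.** The documents give neither the frequency of head impact nor the marker shift it causes, so both are assumptions. Spurious shift b = (difference in prevalence between the groups) × (marker shift in affected patients, in SD). With no effect of inflammation, the chance of P < 0.05 is 1 − Φ(1.960 − b/0.10) + Φ(−1.960 − b/0.10).

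| Difference in prevalence | Marker shift | b | Chance of P < 0.05 |
|---|---|---|---|
| 0 | any | 0 | 5.0% |
| 5 points | 0.25 SD | 0.0125 SD | 5.2% |
| 10 points | 0.5 SD | 0.05 SD | 7.9% |
| 10 points | 1.0 SD | 0.10 SD | 17.0% |

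Against Oslo the difference in prevalence is the full prevalence in the fracture group, if Oslo patients had no recent head impact. Between the fracture groups it is only the gap left by selection.

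**The case against.** The strongest reply is that this is a matter of data fields and a sensitivity analysis, which a journal article may leave to the full protocol, the case report form and the analysis plan. Age is given only as an example of a confounder, and the one-month review collects unspecified further data. Part of this stands: the article does not prove that head impact goes unrecorded. But the narrow exclusion is stated outright, the published schedule has no item that would make up for it, and the causal reading is fixed in the text. If the fields already exist, the sponsor need only say so and state how they will be used.

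A second reply is that the size is wholly assumed. That stands, and at the low end the effect is negligible.

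Three stronger readings are tempting and are not supported:
- **Half or more of Oslo comparisons would be false positives.** A shift of 0.20 SD (20% at 1.0 SD) gives 52%, and 0.30 SD (30% at 1.0 SD) gives 85%. The inputs are assumptions, and four of the five injury markers are not among the listed Oslo assays.
- **Confusion from a head blow places patients in the dementia group.** It affects only the recruitment group. Without evidence of dementia, such a patient goes to the biobank. Any imbalance comes from that removal.
- **Unequal scanning biases the result towards the hypothesis.** The documents say nothing about who is scanned. If confused patients are scanned more, more bleeds are removed from that side, which works against the predicted difference.

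**Conclusion.** The point holds as a limit on interpretation. On the criteria as written, patients with head impact but no CT-proven bleed are in both fracture groups and cannot be identified from the listed data, so mechanical injury cannot be separated from inflammation as a cause of raised injury markers. Against Oslo this applies only to injury markers actually available there. Between the fracture groups it rests on the assumption that head impact makes pre-operative confusion more likely; if head impact is equally common and equally harmful in the two analysed groups, there is no bias.

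The bias is possible, not shown. Assumed shifts of 0.05 to 0.10 SD give about 8% to 17% false positives, larger shifts give more, and 5% prevalence with a 0.25 SD shift leaves the error rate at about 5%. The stroke gap is a secondary instance of the same problem, also without a rate.

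**What to change.** Leave eligibility unchanged. At the one-month notes review that already takes place, record:
- head impact at the fall (yes, no or unknown);
- whether a head CT was done, and its result;
- any recent stroke, if documented.

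Pre-specify that the injury-marker contrasts are repeated without patients who have recorded head impact or recent stroke, with unknown kept as its own category and not merged with no impact. If the result does not hold, qualify the attribution to inflammation. For Oslo, limit this to the injury markers available in that cohort.

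The cost is a few fields from notes already being opened and one extra analysis. Some records will be unknown, and the restricted analysis is smaller. If 10% to 30% of each fracture group were set aside (an assumption), 180 to 140 per group would remain. The difference detectable with 90% power would then rise from 0.32 SD to (1.960 + 1.282) × √(2/180) = 0.34 SD or (1.960 + 1.282) × √(2/140) = 0.39 SD. The restricted analysis should therefore be judged on its estimate and confidence interval, not on whether it stays significant.

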**Inclusion Criteria:**
Patient must have had a confirmed proximal hip fracture requiring an operation and be aged 60 or older at the time of operation;Patient has a pre-operative AMTS of 9 or above; or 4AT score of 0;Patient must be undergoing spinal anaesthesia.

**Exclusion criteria:**
Decision taken not to have hip surgery;Patient has head trauma with bleeding as indicated by a CT scan.Patient has confirmed diagnosis of Parkinson’s disease;Patient not expected to survive beyond 4 weeks;Patient’s fall and subsequent hip fracture caused by acute Stroke, indicated by CT and/or MRI scan and/or clinical examination;Patient already enrolled in a Clinical Trial of an Investigational Medicinal Product (CTIMP).

### Suitable informants

**Inclusion Criteria:**
Individual has a minimum of once a month face-to-face or telephone contact with the patient;Individual is able and consents to complete the IQCODE.

**Exclusion Criteria:**
Individual under 16 years of age.

### Recruitment and consent procedures

A three-phase recruitment process has been guided by conversations with clinical and academic collaborators and previous experience recruiting from this patient group [22].
Research Nurses will collaborate with relevant clinical staff (including but not exclusively the study ward Trauma Co-ordinators and key Emergency Department colleagues) to identify all new hip fracture admissions and screen for pre-recruitment eligibility;Each patient (and where possible their potential suitable informant) will be approached by a Research Nurse who will provide information about the study as soon as clinically appropriate. During this initial approach, the Research Nurse will also assess the mental capacity of the patient;The Research Nurse will approach the patient (where possible) and the identified suitable informant to obtain full written informed consent. In cases where written consent is not possible, ethical approval allows for witnessed verbal consent.

In English trial sites, in line with Principle 1 of the Mental Capacity Act 2005 [23], a potential patient participant will be assumed to have capacity until it is established otherwise. When this is the case and all practical steps to help them to engage in the decision making process have been tried (Principle 2 of Mental Capacity Act 2005), the site trial team will seek a personal consultee. This person will be someone who is engaged in care for the participant (not professionally or for payment) or is interested in his/her welfare and is prepared to be consulted. This may be a family member, carer or close friend, or attorney acting under Lasting Power of Attorney. This person can also act as a suitable informant if they fulfil the inclusion criteria.

If a potential personal consultee is not available or declines to take part, alternatively a nominated consultee will be sought. This will be a person independent of the research study and who is willing to be consulted about the participation of a person who lacks capacity where reasonable steps have been taken to identify a personal consultee. This may be someone who knows the patient in a professional capacity e.g. social worker, ward staff member, paid carer or GP, provided they have no connection to the research study.

In Scottish sites, in line with the Adults with Incapacity Act 2000 [24], where a potential patient participant is assessed not to have capacity, a welfare guardian, welfare attorney or nearest relative will be sought and asked to consent in relation to participation in research (this person will be henceforth known as a legal representative). This procedure will be undertaken once an assessment of capacity has been made in relation to the specific decision regarding the research participation, any barriers to participating in the consent process have been removed and the local research worker feels the individual cannot retain information long enough to use it in order to arrive at a decision.

Legal representatives may be involved in conversations regarding the consenting process. However, they will be asked to differentiate between expressions of their own views and reporting the known values and/or views of the potential patient participant. If the potential participant is unable to consent for himself or herself, then consent will be sought on their behalf from a suitable legal representative.

In cases where gaining full written consent is not possible research workers may take witnessed verbal consent (patients or legal representatives) or agreement (personal consultees). For patients this may be needed due to an inability to write because of injury. With personal consultees or legal representatives this may be due to distance therefore study information may be conveyed over the phone with relevant forms sent via email if appropriate. Where witnessed verbal agreement/consent is taken, full written agreement/consent will be sought where practically possible. A record of all witnessed verbal consent will be added to the patient’s notes.

In both England and Scotland, if during a follow-up assessment the patient is assessed by a local research worker to have regained capacity (a possibility in the case of some cognitive impairments such as delirium); he/she will be approached about continuing to participate in the study and asked to give informed consent. Should they choose to withdraw from the study at this point, the study team reserve the right to retain any data and samples collected up until the point of the patient’s withdrawal. This will be clearly stated in the patient and Consultee (English sites)/Legal Representative (Scottish Sites) Information Sheets.

This three-phase process will be closely monitored to identify trends that might be leading to over or under recruitment from specific groups. For example, if sites are consenting purely via personal consultees (England) or legal representatives (Scotland), monitoring will enable corrective actions and provide information to mitigate these recruitment trends.

### Recruiting patients with fluctuating and/or reduced capacity in England and Scotland

The aims of this study are incompatible with only enrolling patients with minimal or mild confusion. It is important to ensure findings are broadly applicable to those patients with a pre-existing diagnosis or evidence of dementia. Participants who lack capacity to give informed consent must therefore be included. In this situation, the patient’s agreement to participate will still be obtained to their best level of understanding (in line with legislative frameworks in England [23] and Scotland [24]). Where patients in England are assessed as lacking capacity to make a decision regarding their initial or continued involvement with the study, we will seek a personal or nominated consultee agreements [25]. In Scottish study sites where a patient is assessed not to have capacity, a legal representative will be sought and asked to consent in relation to the patient’s participation in the research [26].

